### Analysis response assessment -- efficiency and safety parameters

Efficacy responses are only compiled after the end of the study. However, all patients will be asked to enroll at CASM after participation. Then the current situation and treatment needs can be discussed again. Patients who feel they need urgent medical or psychiatric help during the course of the study are urged to call PrevenTell, or seek psychiatric or medical emergency rooms.

Assessment of clinical safety is carried out continuously. The doctor assesses on the visiting day ECG, OST, lab samples as above and MADRS-S. Unwanted medical events are handled as below. Patients also receive a booklet, a side effects diary, where they can fill in retrospectively what they adverse health effects of treatment they experience, and are encouraged to include it on follow-up.

The annual report, an annual security report to the Swedish Medicines Agency and the Ethics Review Committee, will be done in collaboration with KTA.

## 11. Management of undesired medical events

### Definitions

Unwanted medical events (AE) -- Any unwanted medical event or deterioration of current medical conditions (pedophilia), whether it is related to treatment or not.

Unwanted reactions (AR) -- An unwanted reaction is a harmful and accidental medical reaction to a medical product. For an AE to become an AR, the suspected association between the product and the reaction should be at least possible.

Serious unwanted medical events (SAE) -- Any accidental medical event such as:

- ☐ results in death
- ☐ is life-threatening
- ☐ prompts hospitalization or extended hospitalization
- ☐ results in residual or temporary handicaps
- ☐ results in a congenital injury/birth defect
- ☐ is serious for another reason.

Suspected, unforeseen, serious unwanted reactions (SUSAR) -- A reaction/event that is unexpected, serious, is suspected of being caused by the treatment and which is not described before.

### Assessment of unwanted medical events

Assessment of severity:

**Mild** -- The incident does not affect the subject's life.

**Moderate** -- The event causes deterioration of function with does not affect health. The event causes discomfort and/or inconvenience/obstacles.

**Severe** -- The event causes deterioration of funktion or incapacity for work or poses a health risk to the person.

### Assessment of related links

**Probable** -- Clinical event, including abnormal laboratory analyses, occurs within a reasonable time after administration of degarelix. Unlikely to the event can be attributed to underlying illness or other drugs.

**Possible** -- Clinical event, including laboratory analyses, occurs within a reasonable time after administration of degarelix. The incident is unlikely related to degarelix and can be explained by a drug or underlying disease.

**Not possible to classify** -- The incident cannot be classified because of the absence of information or that the incident is not verified.

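### The causality label *Possible* is defined as unlikely related, and no category exists for unrelated events, so adverse reaction coding is unreliable

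*Supplement*

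**What the plan says.** All the relevant text is in protocol section 11, *Management of undesired medical events*.

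- **AE definition** (*Definitions*): an AE counts "whether it is related to treatment or not".
- **AR threshold** (*Definitions*): "For an AE to become an AR, the suspected association between the product and the reaction should be at least possible".
- **SUSAR** (*Definitions*): among other conditions, the event "is suspected of being caused by the treatment and which is not described before".
- ***Probable*** (*Assessment of related links*): timing is reasonable, and "Unlikely to the event can be attributed to underlying illness or other drugs". The sentence is garbled, but its sense is that another cause is unlikely.
- ***Possible*** (same place): "Clinical event, including laboratory analyses, occurs within a reasonable time after administration of degarelix". The definition continues: "The incident is unlikely related to degarelix and can be explained by a drug or underlying disease".
- ***Not possible to classify*** (same place): "The incident cannot be classified because of the absence of information or that the incident is not verified".

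No fourth category is given there or elsewhere in the documents. The 2019 SAP plans frequency tables of possible side effects by treatment group and defines no causality scale of its own.

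**The concern.** The definition of *Possible* contradicts its label. It describes what a causality scale would normally call unlikely, and it sits at the level that turns an AE into an AR. Because AEs include unrelated events, assessors will meet such events and need somewhere to put them, but the scale offers no place below *Possible*.

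The stake is the safety evidence. Side effects are the first secondary hypothesis (section 5). Adverse events, SUSARs and side effects are the first secondary endpoint (section 6). If the rating that separates an event from a reaction can be read in two ways, a count of reactions by arm has no fixed meaning.

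**Working it through.** No arithmetic applies, because the plan gives no figure on this point. The check sets the three categories against the AR threshold, and then runs five kinds of event through the scale.

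**Categories against the threshold.** Of the three categories, two (*Probable* and *Possible*) meet the threshold by their labels. One (*Not possible to classify*) is reserved for missing or unverified information. None lies below *Possible*.

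**Kinds of event.**

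| Event | Definition that fits | AR by label? | AR by definition? |
|---|---|---|---|
| Reasonable timing, other causes unlikely | *Probable* | Yes | Yes |
| Reasonable timing, drug and another cause both credible | None: *Probable* needs other causes to be unlikely, *Possible* needs the drug to be unlikely | Depends on where the assessor forces it | Yes under the AR sentence, but no category records it |
| Reasonable timing, another cause explains it, drug unlikely | *Possible* | Yes | No |
| Well documented, timing not reasonable | None | Undefined | No |
| Information missing or unverified | *Not possible to classify* | Undefined | Undefined |

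**What follows.**

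1. The third row is the direct conflict. By label the event reaches the threshold. By definition the assessor has just called it unlikely related and can decline to call it an AR.
2. The second row is what *Possible* would ordinarily mean, and it has no home. An assessor may force it into *Probable* or into *Possible*.
3. The fourth row is a further gap. Both causal definitions require reasonable timing, and *Not possible to classify* does not cover a verified event.
4. The direction of error is not fixed. Counting everything labelled *Possible* brings in unrelated events. Discounting it because its definition says unlikely loses any second-row reactions that were placed there.

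**Reach.** The SUSAR definition needs suspected causation and does not cite the scale, so the defect reaches it only if the assessor takes suspicion from the rating. The SAP table is affected only if its possible side effects are chosen by this rating. The SAP does not say, and it may use the word in its everyday sense.

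**The case against.** **Translation.** The *Summary of changes* says that the initial protocol was written in Swedish. The English has plain translation damage: the abbreviation list gives *East* for the osteoporosis tool and *To* for the impulsivity scale, and the sampling list in section 6 has *Tool* where the other laboratory lists have ALAT. The definition of *Probable* is garbled as well. A lost or merged line is a live explanation. This stands as a limit on confidence: the documents do not show that assessors worked under the English wording. It does not remove the contradiction in the text under review.

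**Every event becomes an AR.** A reader might infer that every event that can be classified must become an AR, in both arms. The documents do not support that. An assessor may follow the definition rather than the label, and events without reasonable timing fit neither causal category. That both arms are affected alike is also an inference. Section 7 blinds the investigator, but section 11 does not say who rates causality.

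**Diluted contrast.** A reader might also infer that unrelated events shrink the difference in AR rates between degarelix and placebo by a calculable amount. That requires a pooled rate of any AR per patient, which no section plans to analyse. The SAP speaks of binary variables in frequency tables. If each side effect has its own row, unrelated events of other kinds do not dilute it.

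**Automatic SUSARs.** A reader might infer that any unexpected serious event with another clear cause falls under the 7- or 15-day reporting rule. The SUSAR definition separately requires suspicion that the treatment was the cause, so this does not follow.

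**Limited harm.** All AEs are entered on the AE form, and serious ones go to the sponsor within 24 hours, whatever their causality. This stands, and it keeps the point a secondary one. The AE form is not shown and may already offer an option for unrelated events.

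**Conclusion.** The contradiction is certain on the text shown: *Possible* is defined as unlikely related, nothing lies below it, and it meets the AR threshold. Neither section 11 nor the SAP resolves this. AR classification is therefore unreliable, and SUSAR assessment and the SAP's side-effect table may be.

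The size cannot be put in numbers and the direction of error is uncertain. The primary endpoint and the recording of AEs and serious AEs are not touched.

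Two things could reduce the practical effect: a Swedish original with sound wording, or an AE form that already has an option for unrelated events. Neither is visible in the documents. The point merits correction because it bears on the first secondary endpoint and costs little to mend.

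**What to change.** 1. Compare section 11 with the Swedish original and with the AE form in the CRF. If the original is sound, correct the translation.
2. Reword *Possible* as an event with a reasonable time relation that could also be explained by underlying disease or other drugs.
3. Move the present wording of *Possible* to a new category, *Unlikely / not related*, which also takes events without a reasonable time relation.
4. State under *Definitions* which categories count as AR, and use the same scale on the AE form.
5. Add one line to the SAP saying whether the side-effect table rests on this rating or on all recorded events.

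The cost is about one paragraph of protocol wording and one line in the SAP, plus one tick-box on the AE form if it lacks the option. Any events already rated under the printed wording would need their coding rule stated or their rating checked.

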#### **Reporting of unwanted medical events**

All unwanted medical events are noted in a special AE form in CRF.

Serious unwanted medical events are reported to sponsor on a special SAE form within 24 hours of the fact that we as investigators have become aware of the SAE. Follow-up information describing outcomes and management of the SAE is reported as soon as information is available. The original is inserted into the CRF or trial.

Sponsor is responsible for recording all relevant information about suspicious, unforeseen, serious unwanted reactions and reported to the Swedish Medicines Agency and to the Stockholm Ethics Review Board.

SUSAR, which is deadly or life-threatening, is reported to the Swedish Medicines Agency as soon as possible and no later than 7 days after the incident has become known to sponsor. Relevant follow-up information shall then be submitted within a further 8 days. The rest of SUSAR is reported as soon as possible and no later than within 15 days of being brought to the sponsors' attention.

#### **Follow-up of unwanted medical events**

The subject affected by the incident is followed up until the situation is stable and until the drug can be considered to be metabolized. In case of unacceptable events, the subject is taken out of the study and can then obtain testosterone substitution if necessary.

## 12. Statistics and data handling

### Data handling

The research data is handled differently depending on the type of information it is.

Personal data, identification key and randomization key are kept in a binder marked PRIOTAB-study under strict secrecy in specially locked cabinets in the drug room at CASM during the time the study runs and 10 years thereafter. It is then destructed. In the same place, the CRF binder is stored with completed interview templates, test results from neuropsychology and self-rating forms.

Lab data is saved in the reserve number chart. It can be linked to the person's regular medical records if he chooses to become a patient at CASM.

MRI data is stored registered on the reserve number in the X-ray clinic's journal system RIS/PACS linked to TakeCare. That data will be burned off on CDs stored in the CRF binder.

When the study is completed, the randomization key is broken and data is transmitted by hand to encrypted file processed in statistical programs.

Quality control of data is done by responsible investigators.

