## 6. Endpoints

### Primary endpoint

Primary endpoint is a composite measure 0--15 points, based on estimates scales for various risk factors for sexual abuse. 0--5=low risk. 6--10=medium risk. 11--15=high risk. Primary endpoint thus reflects the risk of child abuse, it is not the actual number of child sexual abuse.

Hypothesis for the primary endpoint of PRIOTAB---RCT: The mean change in the composite risk score between baseline and follow up in the degarelix group is equal to that in the placebo group.

The null hypothesis will be tested with a two---sided t---test.

**Comment:** There are no established measures for the risk of sexual abuse of children in pedophilia (21). The SBU proposes in its 2011 report (22) that endpoint for child sexual abuse should be the number of child sexual abuse. The fact that we refrain from using the proposed endpoint is partly because the measure would be very difficult to get a good idea of-- the under-reporting in research studies presumed to be significant and information taken detour through the judiciary, the number of convictions, probably does not reflect the reality (15). It would also require very large data collections. Furthermore, we find it ethically questionable, with concern for the individual children, to design a study so that it will collect new cases of child sexual abuse. There is therefore a need for a surrogate measure that more focuses on the risk.

We have therefore created this composite measure based on risk factors for sexual abuse. It is based on the results of the only meta-analysis in the field (16). The four risk factors with the highest predictive value of sexual assault that are published in that study (deviant sexual orientation, absorption in sexual thoughts, poor self-control and lack of empathy) are those whose extent may also be presumed to be sensitive to treatment. We also add a fifth item, self-perceived risk. Thus 5 items. Based on the result of estimates of each one, they are scored on a scale of 0--3 points (0=not clinically significant, 1=clinically significant of small scope, 2=clinically significant in medium scope, 3=clinically significant to a high extent). The results are summarized and aggregated points in this composite measure are thus 0--15p. The composite measure is designed by the research team and will be validated in PRIOTAB's first part, PRIOTAB-CC. We believe it has high clinical relevance.

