The p---values used at the interim analysis and at the possible final analysis will be 0.0294 [Pocock SJ, Group sequential methods in the design and analysis of clinical trials. *Biometrika*, 1977, 64 (2): 191–199]. These smaller p---values will preserve the overall level of the test at 0.05.

The blinding will be preserved by not disclosing the treatment group assignment to any of the parties involved, which comprise the patients, the doctors, and the analysts.

Patients that drop out will be included in an intention to treat analysis. Patients with missing values for the risk score at any time point will be excluded from the analysis. The analyses will be performed under the assumption that the missing data generating process is at random [Rubin DB. *Inference and missing data*. *Biometrika*, 1976, 63 (3): 581–592]. To assess the plausibility of this assumption, information on the reasons missingness will be elicited from the patients, doctors, or any other source available.

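### The protocol places the code break before, or together with, hand entry of the paper data, and nothing requires entry, scoring, checking and database lock to be finished blind

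*Supplement*

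**What the plan says.** The protocol, section 12, Data handling, is the only place that describes how data reach the analysis file. The source data are on paper: "In the same place, the CRF binder is stored with completed interview templates, test results from neuropsychology and self-rating forms". The place meant is the locked storage in the drug room that also holds the identification and randomisation keys. The section continues: "When the study is completed, the randomization key is broken and data is transmitted by hand to encrypted file processed in statistical programs". Its last sentence is: "Quality control of data is done by responsible investigators".

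Four other places bear on the point.

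- Protocol section 10, on response assessment: "Efficacy responses are only compiled after the end of the study".
- Protocol section 6, Primary endpoint, on the five components of the composite: "Based on the result of estimates of each one, they are scored on a scale of 0--3 points". It does not say who does the grading, when, or under what blinding.
- Protocol section 12, Statistical analysis: "The blinding will be preserved by not disclosing the treatment group assignment to any of the parties involved". The parties listed are patients, doctors and analysts. No end point is given for this.
- The SAP of 25 June 2019 says that the analysis follows the protocol. It does not mention data entry, checking, lock or code break.

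**The concern.** In a double-blind trial the code is normally opened only after the data have been entered, checked and locked, so that nobody who can still change a value or exclude a man knows his arm. The order in this protocol appears to be the reverse.

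The endpoint leaves room for judgement. Each item is graded 0-3 against verbal anchors, and the protocol text gives no numerical cut-offs. The empathy item is listed with two instruments, so some rule is needed to turn two results into one grade. Membership of the primary analysis also depends on a judgement: the population is men who took the study drug and whose questionnaires allow a full risk assessment, and men with a missing risk score at any time point are excluded. Grading, query resolution and these exclusions are the decisions that blinding should protect. If they can be made after the code is open, a reader of the results cannot rule out that knowledge of the arm influenced them.

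**Working it through.** The point concerns the order of procedures, so the main check is to set the sections side by side.

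**1. Order of code break and entry.** Data handling names the code break first and the hand transfer second, in one sentence and both at study completion. The two are joined by a plain conjunction. The natural reading is code break, then entry. The lenient reading is that they happen together. Neither puts entry first.

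**2. Quality control.** The sentence comes directly after the code break and names the investigators. It has no timing and no blinding condition. Section 7 says investigators and researchers are blind during conduct; nothing extends that to the checking stage.

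**3. Scoring.** Section 10 has efficacy responses compiled only after the end of the study, the same point at which the key is broken. So scoring either falls in the unblinded period or is not protected from it. The text does not say which.

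**4. Blinding statement.** The statistics section says that doctors and analysts are not told the assignment. If the key is broken at or before data entry and investigators then check the data, some further step is needed to keep them and the analysts blind. None is described, so the two statements conflict as written.

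**5. Interim data.** Section 12 plans an efficacy and safety analysis once 20 individuals have passed through the study. Their data must be entered before study completion, so the sequence in Data handling cannot cover all the data. No blind process is described for this earlier entry either.

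**6. Amount of data exposed.** Inputs: 60 men (section 12, Study size), 5 items (section 6), and 2 visits, because the SAP defines the primary test on change from baseline to two weeks.

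- Item scores feeding the primary test: 60 x 2 x 5 = 600 at most.
- Counting the ten-week visit gives 60 x 3 x 5 = 900, but those extra scores do not enter the primary test.

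**7. Illustration of size.** The plan's own sample-size figure reproduces: 2 x (1.96 + 0.842)^2 x 3^2 / 5^2 = 5.65, rounded up to 6 per arm. It has no bearing on the order of steps, but it supplies the SD of 3. With 30 men per arm and the two-sided 0.0294 level:

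- Critical difference = t x SD x sqrt(2/n) = 2.23 x 3 x sqrt(2/30) = 1.73 points (58 degrees of freedom, 0.0147 in each tail).
- Assumed error: one point on one item, in the same direction, in 5 of 30 men in one arm. Shift in the between-arm difference = 5/30 = 0.17 points.
- Ratio to the critical difference: 0.17/1.73 = about 10%.
- Ratio to the plan's smallest relevant difference of 5 points: 0.17/5 = about 3%.

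The error rate of 5 in 30 is an assumption. Nothing in the documents gives one.

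**The case against.** The strongest reply is that this is loose wording. The protocol was first written in Swedish, the English shown is rough in many places, and clause order in such text is weak evidence of procedural order. The statistics section states a safeguard outright, and analysts can be blind only if their file does not reveal the arm. The answers are put on paper while investigators are blind, and the Summary of changes says that the measures, their interpretation and their scoring were not altered after the trial began in March 2016.

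Part of this stands. The order is the natural reading but not an explicit one, and fixed scoring rules limit discretion. But fixed rules are not the same as rules applied blind, and the safeguard is stated without any step that would deliver it. Even on the lenient reading, nothing requires blind completion and lock before the code break.

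Four stronger readings are tempting, and the documents do not support them.

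- A reader might infer that scoring and quality control are planned with the arms visible. The text gives no timing for quality control, and Data handling does not mention scoring.
- A reader might infer that blinded investigators use the cabinet holding the key. The key and the CRF binder are stored in the same place, but who opens that storage is not stated, and section 7 says only the research nurse knows the allocation.
- A reader might infer that the analyses were not fixed before unblinding. The Summary of changes says the secondary endpoints and methods were added to the SAP before unblinding, and that the primary analysis was performed as in the 2014 plan. The order of data entry does not undo that.
- A reader might infer that the primary test rests on scores from all three visits. It uses two.

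**Conclusion.** The point holds as a conflict in the plan. Data handling puts the code break before, or together with, hand entry and attaches no blinding condition to the investigators' quality control. The statistics section says doctors and analysts are not told the assignment. No section shown requires entry, scoring, query resolution, population decisions and lock to be completed blind, whether at the end of the study or for the interim data.

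Up to 600 item scores feed the primary test, and none has a stated protection at these steps. The effect on the result cannot be estimated from the documents. The shift of 0.17 points, about a tenth of the critical difference, is illustrative only; it assumes an SD of change of 3, 30 analysed men per arm, and one-point errors in the same direction in 5 men of one arm. It is not evidence that bias occurred.

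The conclusion rests on the protocol and SAP as shown. The CRF, which may hold scoring cut-offs, is not among them.

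**What to change.** Rewrite the Data handling sequence so that these steps come before the key is broken, in this order:

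1. Entry of the paper data with verification, such as double entry.
2. Derivation of the 0-3 item scores by a fixed written rule.
3. Quality control and query resolution by investigators who are still blind.
4. Decisions on who has a full risk score and so enters the analysis.
5. A documented, dated database lock.

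State that the interim data on 20 men go through the same blind process. Give the statement on non-disclosure to doctors and analysts an explicit end point, so that it agrees with the revised sequence. State that only the research nurse has access to the randomisation key, and store it apart from the CRF binder. Repeat the lock and code-break order in the SAP.

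If practice already followed this order, dated records of the lock and the code break would show it. The cost is a few sentences and a separate locked drawer, plus the time for double entry if that was not already planned. The sample size and the primary test do not change.
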